## **3. Study Design**

This is a prospective, multi-center, phase 2 clinical study to investigate the efficacy and tolerability of VAH regimen in patients with R/R AML. Approximately 96 subjects will be enrolled to receive VAH regimen for salvage therapy. The study design is illustrated in Figure 1

Subjects with R/R AML will be screened for eligibility. Medical history evaluation, vital sign, physical examination, ECOG performance status, blood and urine sampling

for laboratory tests, electrocardiogram, chest imaging examination as well as bone marrow (BM) assessment will be performed to determine study eligibility.

After enrolment, patients will be assigned to the trial therapy. For VAH treatment, VEN begins at 100 mg on day 1 and increases stepwise over 3 days to reach the target dose of 400 mg (100 mg, 200 mg, 400 mg); dosing is continued at 400 mg per day from day 4 through day 14; AZA (75 mg/m^2) is administered subcutaneously on days 1-7, and HHT (1 mg/m^2) on days 1-7. VEN dose will be reduced by at least 50% in the patients receiving concomitant moderate or strong CYP3A4 inhibitors (eg, azole antifungals). FLT3 inhibitors are allowed in the patients with FLT3 mutations. Donor lymphocyte infusion (DLI) is administered at day 15 after the initiation of the trial therapy for the relapse patients after allo-HSCT. Once acquiring CRc, the patients are recommended to receive allo-HSCT if donors are available. If donors are unavailable, patients will receive one course of original therapy again and sequential cytarabine-based consolidation therapy. In addition, for the patients undergoing allo-HSCT, sorafenib maintenance post-transplantation was recommended regardless of FLT3 being mutated or not. If patients do not obtain CRc after two courses of the trial therapy, they will proceed to allo-HSCT if donors are available, and patients receive other salvage therapy based on patients' personal preferences after full discussion with physicians if donors are unavailable.

For response assessments, bone marrow is evaluated on cycle 1 day 28 and again 1-2 weeks after hematological recovery if the day 28 bone marrow is aplastic. Subsequent bone marrow evaluations are done before and after cycles 2, and then as clinically needed. Morphological and MRD assessments are done during each bone marrow assessment. CR is defined as an absolute neutrophil count of more than 1000 cells per cubic millimeter, a platelet count of more than 100,000 per cubic millimeter, red-cell transfusion independence, and bone marrow with less than 5% blasts. CRi is defined as all the criteria for CR, except for neutropenia (absolute neutrophil count,  $\leq 1000$  per cubic millimeter) or thrombocytopenia (platelet count,  $\leq 100,000$  per cubic millimeter). Partial remission (PR) is a minimal residual disease of 5-25% with a greater than 50% decrease in leukemic blast percentage. Non-remission (NR) is defined as a failure to

obtain CRc or PR. CRc comprised CR and CRi, and overall response rate (ORR) includes CRc and PR. The MRD level of 0.01% is used as a threshold to distinguish MRD positive (MRD+) from MRD negative (MRD).

The clinical data cutoff date is June 30, 2022. Criteria for removing patients from trial therapy includes the development of intolerable adverse events related to study treatment (determined by the treating physician), patient withdrew informed consent, and completion of the protocol therapy and evaluation period.

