## **2. Study objectives**

### **2.1 Primary Objective**

The primary endpoint is CRc rate after 2 cycles of trial treatment.

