#### **4.1.2 Inclusion Criteria**

Subjects eligible for enrolment in this study must meet all of the following criteria:

1. Patients with R/R AML

Refractory AML is defined as no CRc and a reduction in bone marrow blasts of less than 50% after one cycle or no CRc after two cycles. Relapsed AML is defined as recurrence of blasts in the peripheral blood or bone marrow blasts  $\geq 5\%$  or development of extramedullary disease after achieving CRc.

2. Age 18 to 65 years old with ECOG performance status of 0-2

3. Sign informed consent form, have the ability to comply with study and follow-up procedures.

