## **6. Efficacy Assessments**

### **6.1 Definitions**

- Relapse is defined as reappearance of leukemic blasts in the peripheral blood or  $\geq$  5% blasts in the BM as pirate or biopsy not attributable to any other cause or reappearance or new appearance of extramedullary leukemia after achieving CRc.

CR is defined as BM blasts <5%; absence of circulating blasts and blasts with Auer rods; absence of extramedullary disease; ANC  $\geq 1.0 \times 10^9/\text{L}$  and PLT  $\geq 100 \times 10^9/\text{L}$ .

CRi is defined as all CR criteria except for incomplete hematologic recovery with neutropenia  $< 1.0 \times 10^9/\text{L}$  and/ or thrombocytopenia  $< 100 \times 10^9/\text{L}$ .

PR is defined as a minimal residual disease of 5-25% with a greater than 50% decrease in leukemic blast percentage.

NR is defined as a failure to obtain CRc or PR.

CRc comprises CR and CRi.

ORR includes CRc and PR.

The MRD level of 0.01% is used as a threshold to distinguish MRD positive (MRD+) from MRD negative (MRD).

OS is defined as the time from treatment until death or censored at the last follow-up.

EFS is defined as the time from treatment until documented failure to achieve CRc, relapse after CRc, or death from any cause, whichever occurred first.

DFS is defined as the time from the date of CRc until relapse, death from any cause, or censored at the last follow-up.

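### The primary endpoint CRc rests on two conflicting definitions of CR and CRi, with nothing to say which governs; under one of them some eligible patients can already meet CRc at entry

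*Protocol*

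**What the plan says.** Section 2.1 states: "The primary endpoint is CRc rate after 2 cycles of trial treatment". Section 6.1 adds that "CRc comprises CR and CRi". Whatever CR and CRi mean therefore fixes the primary endpoint.

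The Protocol defines them twice.

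- **Section 3, repeated in the synopsis.** CR needs "an absolute neutrophil count of more than 1000 cells per cubic millimeter", platelets above 100,000 per cubic millimetre, and "red-cell transfusion independence, and bone marrow with less than 5% blasts". The CRi text reads "CRi is defined as all the criteria for CR, except for neutropenia" or thrombocytopenia, so transfusion independence carries over to CRi.
- **Section 6.1.** "CR is defined as BM blasts <5%; absence of circulating blasts and blasts with Auer rods; absence of extramedullary disease", with neutrophils of at least 1.0 and platelets of at least 100 × 10⁹/L. CRi keeps everything except the counts.

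Eligibility (Section 4.1.2 and the synopsis) accepts relapse shown by blood blasts, by marrow blasts of 5% or more, or by "development of extramedullary disease after achieving CRc". Any one of these is enough, and Section 4.1.3 does not exclude patients with a clear marrow.

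**The concern.** Neither definition summarises the other, because each contains a requirement that the other lacks. Ten centres could classify the same patient differently. The only adjudication committee described (Section 7) rules on the relatedness of adverse events, not on response. With both definitions in force, the choice could also be made after the results are known.

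The trial compares one arm with a fixed historical 45%, so no control group absorbs a shift in definition. The effect reaches further than CRc. EFS ends at failure to reach CRc, DFS starts at the date of CRc, and Sections 3 and 5.2 use CRc status to separate the later treatment paths.

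**Working it through.** **The plan's own figure.** Inputs from Section 11.1: p0 = 0.45, p1 = 0.60, 5% significance, 80% power. Section 11.4.2.2 makes tests two-sided.

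- n = [(1.960·√(0.45·0.55) + 0.8416·√(0.60·0.40)) / 0.15]² = 85.5, so 86.
- With the null variance in both terms: [(1.960 + 0.8416)·√(0.45·0.55) / 0.15]² = 86.3, so 87, as stated.
- Dropout: 87 × 1.1 = 95.7, so 96 as stated (87/0.9 = 96.7 would give 97).

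The sample size reproduces and is not in question here.

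**The definitions side by side.**

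| Criterion | Section 3 and synopsis | Section 6.1 |
|---|---|---|
| Marrow blasts below 5% | required | required |
| Red-cell transfusion independence | required for CR and CRi | not mentioned |
| No circulating blasts | not mentioned | required for CR and CRi |
| No Auer rods | not mentioned | required for CR and CRi |
| No extramedullary disease | not mentioned | required for CR and CRi |
| Count cut-offs for CR | strictly above | at or above |

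**Patients who change class** (all with marrow blasts below 5%).

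1. Still needs red cells, no residual disease elsewhere. Section 6.1: CR if both counts recover, CRi if not; CRc either way. Section 3: not CRc.
2. Transfusion independent, with persistent extramedullary disease or circulating blasts. Section 3: CRc. Section 6.1: not CRc.
3. Enrolled with relapse shown only by extramedullary disease or blood blasts, and transfusion independent. Before the first dose this patient meets Section 3 CR or CRi, and at the same time is relapsed under Section 4.1.2. If the same findings persist at the response assessment, CRc is counted although the disease that led to enrolment has not cleared. Under Section 3, DFS then starts in a patient who still has leukemia, whereas under Section 6.1 the same patient is an EFS failure.

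A neutrophil count of exactly 1000 or a platelet count of exactly 100,000 is CRi in Section 3 and CR in Section 6.1, so it is CRc in both.

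**Scale, by assumption.** The Protocol gives no share of such patients and no success threshold. I take the smallest r with P(X ≥ r | 96, 0.45) ≤ 0.025. This is r = 54, with tail probability 0.0175 and power 0.804 at 60%. If k patients count as CRc whatever the treatment does and the rest respond at 45%, the chance of success is P(Bin(96 − k, 0.45) ≥ 54 − k) and the expected rate is (k + 0.45(96 − k))/96.

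| k | Expected CRc rate | Chance of at least 54/96 |
|---|---|---|
| 0 | 45.0% | 1.8% |
| 2 | 46.1% | 2.9% |
| 5 | 47.9% | 5.6% |
| 10 | 50.7% | 14.9% |

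The opposite direction is equally open. If the transfusion criterion lowered a true 60% to 57% or 55% (again assumed), the chance of reaching 54/96 would fall from 80.4% to 60.1% or 44.4%.

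**The case against.** The best defence is that Section 3 is shorthand, that no haematologist would record remission in a patient with visible extramedullary disease or blood blasts, and that such a patient plainly meets the Protocol's own definition of relapse. The baseline route is also narrow, since it needs a marrow below 5% and transfusion independence together. This limits how often case 3 arises. It does not say which text governs, and it leaves case 1 untouched, where Section 3 is the stricter text. An analysis plan that is not shown does not resolve it either, because the Protocol itself fixes both definitions.

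A reader might infer more than the document supports:

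- **That Section 3 is the looser definition and inflates CRc.** It is looser on residual disease and stricter on transfusion.
- **That every isolated extramedullary relapse is CRc at entry.** Patients who need red cells are not.
- **That five patients, 5/96 = 5.2 points, lift a 45% null rate to about 50%, with a 13.1% chance of reaching 54/96.** Five patients who always count add only 0.55 × 5/96 = 2.9 points, because 45% of them were expected to respond anyway; the chance is 5.6%. Reaching 50% takes 4.8/0.55 = 8.7, about nine patients.
- **That patients can be reclassified from data already held.** Section 7.4 lists white cells, neutrophils, hemoglobin and platelets, but no blood blast count and no transfusion record. Chest imaging is the only imaging listed, and no dedicated extramedullary assessment is scheduled.
- **That the cut-off signs or the PR wording affect the primary endpoint.** They do not.

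**Conclusion.** The contradiction is plain on the text and must be resolved before CRc is analysed. The primary endpoint has two rules, neither uniformly stricter, and no stated precedence. Some eligible patients can meet one of the rules at entry while in relapse, which also leaves EFS and DFS without a coherent meaning for them.

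The size and net direction cannot be determined from the Protocol. The figures above rest on assumed patient counts or rates and an assumed 54/96 threshold. They show that a handful of patients matters, not that the result is biased by any given amount.

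Two wording points are minor and leave CRc unchanged: the strict versus non-strict cut-offs, and "PR is defined as a minimal residual disease of 5-25% with a greater than 50% decrease in leukemic blast percentage". The latter cannot stand beside the 0.01% MRD threshold in the same section; a marrow blast percentage is evidently meant. It bears on PR, NR and ORR only.

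**What to change.** 1. Put one governing definition of CR and CRi in the synopsis, Section 3 and Section 6.1, under which a patient with persisting extramedullary disease or circulating blasts cannot count as CRc.
2. State once whether red-cell transfusion independence is required for CR and for CRi, in line with the definition behind the 45% benchmark. That source is not available here, so the sponsor must check it.
3. Fix the choice before the CRc results are analysed, and apply it to all patients. If patients have already been assessed, report CRc under both definitions as a sensitivity analysis, so that the choice cannot be suspected of following the data.
4. Make sure the CRF captures transfusions, blood blasts and extramedullary status at baseline and at each response assessment.
5. Align the cut-off signs and correct the PR wording.

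The cost is Protocol and CRF wording plus a re-review of patients already assessed. The sample size does not change. Where transfusions, blood blasts or extramedullary status were not recorded, reclassification may be incomplete, and the report should say for how many patients.

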**Figure 1 Study Schema**

[figure not shown]

AML=acute myeloid leukemia; ECOG= Eastern Cooperative Oncology Group; CRc= composite complete remission; VAH=venetoclax+azacitidine+homoharringtonine.

## **4. Subject Selection Criteria**

### **4.1 Subject Selection Criteria**

#### **4.1.1 Number of Subjects**

Approximately 96 subjects will be enrolled to receive VAH regimen for salvage therapy.

#### **4.1.2 Inclusion Criteria**

Subjects eligible for enrolment in this study must meet all of the following criteria:

1. Patients with R/R AML

Refractory AML is defined as no CRc and a reduction in bone marrow blasts of less than 50% after one cycle or no CRc after two cycles. Relapsed AML is defined as recurrence of blasts in the peripheral blood or bone marrow blasts  $\geq 5\%$  or development of extramedullary disease after achieving CRc.

2. Age 18 to 65 years old with ECOG performance status of 0-2

3. Sign informed consent form, have the ability to comply with study and follow-up procedures.

#### **4.1.3 Exclusion Criteria**

Subjects meeting any of the following criteria are ineligible for this study:

1. Acute promyelocytic leukemia (AML subtype M3)

2. Previous exposure to the treatment of VEN-based regimen

3. Cardiac dysfunction (particularly congestive heart failure, unstable coronary artery disease and serious cardiac ventricular arrhythmias requiring antiarrhythmic therapy)

4. Respiratory failure (  $\text{PaO}_2 \leq 60\text{mmHg}$  )

5. Hepatic abnormalities (total bilirubin  $\geq 2$  times the upper limit of normal [ULN], ALT or AST  $\geq 2$  times the ULN)

6. Renal dysfunction (creatinine  $\geq 2$  times the ULN or creatinine clearance rate  $< 30$  mL/min)

7. ECOG performance status 3, 4 or 5

8. Substantial history of neurological, psychiatric, endocrine, metabolic, immunological, or any other medical condition not suitable for the trial (investigators' decision)

9. Active acute or chronic graft-versus-host disease (GVHD). Active acute GVHD or chronic GVHD was defined as GVHD requiring either at least 1 mg/kg per day of prednisone (or equivalent) or treatment beyond systemic corticosteroids.

10. Patients with pregnancy

11. Uncontrolled active infection

## 12. Clinically significant coagulation abnormalities

### **4.2. Withdrawal Criteria**

Subjects are free to withdraw consent and discontinue participation in the study at any time and without prejudice to future treatment. A subject's participation in the study may be discontinued at any time at the investigator's discretion. Justifiable reasons for a subject to be withdrawn from the study include:

1. Inability to fully comply with the study protocol
2. Unacceptable toxicity
3. Best interest of the subject based upon the investigator's discretion
4. At the request of the study subject at any time and for any reason

Subjects will be followed up unless the informed consent is withdrawn. The reason for withdrawal from study participation and the date must be documented in the case report form (CRF). The investigator must complete the last visit, including vital signs, physical examination, laboratory tests, disease status and AE assessment, all of which must be documented in the CRF.

## **5. Study Procedures**

### **5.1 Screening**

Subjects with R/R AML will be screened for eligibility. Medical history evaluation, vital sign, physical examination, ECOG performance status, blood and urine sampling for laboratory tests, electrocardiogram, chest imaging examination as well as BM assessment will be performed to determine study eligibility, all of which must be performed  $\leq 3$  days prior to randomization.

### **5.2 Study Treatment**

#### **VAH salvage therapy**

VEN begins at 100 mg on day 1 and increases stepwise over 3 days to reach the target dose of 400 mg (100 mg, 200 mg, 400 mg); dosing is continued at 400 mg per day from day 4 through day 14; AZA (75 mg/m^2) is administered subcutaneously on days 1-7, and HHT (1 mg/m^2) on days 1-7.

VEN dose will be reduced by at least 50% in the patients receiving concomitant moderate or strong CYP3A4 inhibitors (eg, azole antifungals). FLT3 inhibitors are allowed in the patients with FLT3 mutations. DLI is administered at day 15 after the initiation of the trial therapy for the relapse patients after allo-HSCT. Once acquiring CRc, the patients are recommended to receive allo-HSCT if donors are available. If donors are unavailable, patients will receive one course of original therapy again and sequential cytarabine-based consolidation therapy. In addition, for the patients undergoing allo-HSCT, sorafenib maintenance post-transplantation was recommended regardless of FLT3 being mutated or not. If patients do not obtain CRc after two courses of the trial therapy, they will proceed to allo-HSCT if donors are available, and patients receive other salvage therapy based on patients' personal preferences after full discussion with physicians if donors are unavailable.

### **5.3 Follow-up**

The clinical data cutoff date is June 30, 2022. Disease assessment including routine blood and BM assessment will be regularly performed post-salvage therapy. For response assessments, bone marrow is evaluated on cycle 1 day 28 and again 1-2 weeks after hematological recovery if the day 28 bone marrow is aplastic. Subsequent bone marrow evaluations are done before and after cycles 2, and then as clinically needed. Adverse events are recorded up to 4 weeks after the discontinuation of the trial therapy, and are graded according to the National Cancer Institute Common Terminology Criteria for Adverse Events version 4.0.

## **6. Efficacy Assessments**

### **6.1 Definitions**

- Relapse is defined as reappearance of leukemic blasts in the peripheral blood or  $\geq$  5% blasts in the BM as pirate or biopsy not attributable to any other cause or reappearance or new appearance of extramedullary leukemia after achieving CRc.

CR is defined as BM blasts <5%; absence of circulating blasts and blasts with Auer rods; absence of extramedullary disease; ANC  $\geq 1.0 \times 10^9/\text{L}$  and PLT  $\geq 100 \times 10^9/\text{L}$ .

CRi is defined as all CR criteria except for incomplete hematologic recovery with neutropenia  $< 1.0 \times 10^9/\text{L}$  and/ or thrombocytopenia  $< 100 \times 10^9/\text{L}$ .

PR is defined as a minimal residual disease of 5-25% with a greater than 50% decrease in leukemic blast percentage.

NR is defined as a failure to obtain CRc or PR.

CRc comprises CR and CRi.

ORR includes CRc and PR.

The MRD level of 0.01% is used as a threshold to distinguish MRD positive (MRD+) from MRD negative (MRD).

OS is defined as the time from treatment until death or censored at the last follow-up.

EFS is defined as the time from treatment until documented failure to achieve CRc, relapse after CRc, or death from any cause, whichever occurred first.

DFS is defined as the time from the date of CRc until relapse, death from any cause, or censored at the last follow-up.

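### PR is defined on an MRD scale while CR and CRi are defined on marrow blasts, so PR, NR and ORR can be misclassified in either direction

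*Protocol*

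**What the plan says.** The response criteria appear three times in the protocol: in the Synopsis (study design row), in Section 3 and in Section 6.1. All three put PR on MRD. Section 3 reads "Partial remission (PR) is a minimal residual disease of 5-25% with a greater than 50% decrease in leukemic blast percentage"; Section 6.1 reads "PR is defined as a minimal residual disease of 5-25% with a greater than 50% decrease in leukemic blast percentage".

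The neighbouring classes use marrow morphology. In Section 6.1, "CR is defined as BM blasts <5%; absence of circulating blasts and blasts with Auer rods; absence of extramedullary disease", together with neutrophil and platelet thresholds. For the second class, "CRi is defined as all CR criteria except for incomplete hematologic recovery with neutropenia" or low platelets. Neither class has an MRD condition.

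Two further terms are built on PR: "NR is defined as a failure to obtain CRc or PR", and "ORR includes CRc and PR".

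MRD has a separate role: "The MRD level of 0.01% is used as a threshold to distinguish MRD positive" from negative. Section 3 lists morphology and MRD as two assessments made at each marrow examination. No order of precedence between CRc and PR is given.

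Sections 6.2 and 6.3 name CRc after two cycles as the primary endpoint, and safety, OS, EFS, DFS and relapse as secondary endpoints. ORR, PR and NR are defined but not listed as endpoints.

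**The concern.** A set of response classes should divide one scale, or state clearly how two scales combine. Here the CR and CRi ceiling is 5% on marrow blasts, and the PR floor is 5% on MRD. The two measurements come from the same marrow but need not agree, so the boundary does not join up.

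The protocol's other disease-burden thresholds use blasts. Relapse is at least 5% marrow blasts (Sections 4.1.2 and 6.1). Refractory disease at entry is in part "no CRc and a reduction in bone marrow blasts of less than 50% after one cycle". The second half of the PR sentence also speaks of blasts. This suggests, without proving, that marrow blasts were meant throughout.

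At stake are the PR, NR and ORR figures that the trial would report and, across ten centres, whether the same patient would be classed the same way everywhere. The primary endpoint is exposed only indirectly.

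**Working it through.** **1. The plan's own figure.** The protocol gives no number for PR, NR or ORR. Its one design figure is 87 patients, rising to 96 with 10% dropout (Section 11.1), for CRc of 60% against 45%, with 5% significance and 80% power. Section 11.4.2.2 makes tests two-sided.

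- n = [(1.960·√(0.45·0.55) + 0.842·√(0.60·0.40)) / 0.15]² = 85.5, so 86.
- With the null variance in both terms, n = [(1.960 + 0.842)·√(0.45·0.55) / 0.15]² = 86.3, so 87.
- 87 × 1.1 = 95.7, so 96.

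The stated figure is reproduced. PR does not enter it, so nothing below changes the sample size or the power.

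**2. The written rules applied to single patients.** The rules are those of Section 6.1. All values are illustrative.

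| Patient | Fall in blasts | Class as written | Class if PR is read on marrow blasts of 5-25% |
|---|---|---|---|
| (a) Blasts 40% to 4%, all other CR or CRi criteria met, MRD 6% | (40−4)/40 = 90% | CRc and PR | CRc |
| (b) Blasts 60% to 8%, MRD 3% | (60−8)/60 = 86.7% | NR | PR |
| (c) Blasts 40% to 4%, circulating blasts or extramedullary disease present, MRD 10% | 90% | PR | NR |

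Type (b) also arises when MRD is above 25%. For example, blasts from 40% to 18% are a 55% fall; with MRD of 30% the patient is NR as written.

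**3. A systematic check.** I crossed seven marrow blast values (1, 4, 5, 10, 18, 25, 30%), eight MRD values (0.005, 0.5, 4, 5, 10, 18, 25, 30%) and blood/extramedullary status (clear or not), with baseline blasts assumed at 40%. This gives 7 × 8 × 2 = 112 profiles. They are not patient frequencies.

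- Both CRc and PR as written: 8 (type a).
- NR as written, PR on blasts: 24 (type b).
- PR as written, NR on blasts: 8 (type c).
- Same class either way: 8 CRc, 24 PR and 40 NR.
- No class as written: 0.

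The total is 8 + 24 + 8 + 8 + 24 + 40 = 112. With PR on marrow blasts, every profile has exactly one class.

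**4. Size.** Over the 96 planned patients, one misplaced patient is 1/96 = 1.04 percentage points. Against a blast-based PR, ORR as written is off by (number of type c − number of type b)/96. Type (a) adds nothing to that difference, because ORR counts a patient who meets either class once. The documents do not say how often MRD and morphology disagree in these ways, so neither the size nor the sign of the net error can be computed.

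**5. Reach into the listed endpoints.** A type (a) patient meets CRc on the text. If a site nevertheless records PR only, CRc falls by 1.04 points, EFS gains an event through its failure-to-achieve-CRc component, and the patient leaves DFS, which starts at CRc.

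**The case against.** The strongest reply is that nothing the trial plans to test depends on PR. The primary endpoint, the historical comparison, the sample size and the EFS failure component all use CRc, and the efficacy analysis in Section 11.4.2.2 mentions none of PR, NR or ORR. This is correct, and it limits the importance of the point.

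It can also be said that sites would probably read the phrase as residual blasts, since the 5% floor meets the CR ceiling and the sentence goes on to speak of blasts. That is plausible. But the same wording stands in three places beside a separate MRD definition at 0.01%, so a site that applies the text as written is not at fault.

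Three stronger readings are tempting, and the documents do not support them.

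- *Some patients are left without a class.* They are not: NR is the remainder. The fault shows as wrong NR assignments.
- *The overlap distorts ORR or CRc by itself.* It does not. ORR is a union, and CR and CRi carry no MRD condition. CRc is affected only through a recording choice.
- *ORR is understated by some number of points.* No discordance rate is given, and type (c) patients move ORR the opposite way, so the direction is open.

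Lastly, a blast-based PR would still leave a patient with marrow blasts below 5% and persisting circulating blasts or extramedullary disease as NR, despite a large fall. That is so. It would then follow from a single consistent scale, and the sponsor should confirm that it is intended.

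**Conclusion.** The point holds as a wrong rule with limited reach. The protocol fixes PR on a different measure from CR and CRi, in all three places. Applied literally, it sends some patients with a clear blast response to NR, lets some CRc patients also qualify as PR without a precedence rule, and admits as PR some patients whose marrow is below 5% but whose disease persists elsewhere.

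PR, NR and ORR can therefore be misclassified in either direction, by 1.04 points per patient at N = 96, with a frequency that the documents do not give. The sample size is unaffected. The primary CRc rate, EFS and DFS are affected only if a site records an overlap patient as PR. It should be corrected, but it does not threaten the primary analysis.

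The conclusion assumes that MRD and morphological blasts are distinct measurements, as Section 3 presents them. Type (c) also relies on the fuller CR definition in Section 6.1, which requires absence of circulating blasts and of extramedullary disease.

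**What to change.** In the Synopsis, Section 3 and Section 6.1:

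- State PR on bone marrow blasts of 5-25%, keep the requirement of a fall of more than 50% in blasts, and name the baseline marrow from which the fall is measured. The protocol does not now name one.
- State that each patient is assigned one class, in the order CR, CRi, PR, NR.
- Use MRD only for the positive/negative split at 0.01%.

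The cost is a wording change in three places. Morphology is already assessed at each marrow examination, so no new procedure or data item is needed, and the sample size does not change. If any patient has already been classified, the class should be re-derived from the recorded marrow blast percentages.
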